### 12.2 Criteria for Discontinuation of Protocol Treatment/Intervention

In the absence of treatment delays due to adverse event(s), treatment may continue until one of the following criteria applies:

- Disease progression during neoadjuvant treatment which precludes surgery (e.g., tumor perforation that prohibits completion of treatment or treatment as designated per Arm or detection of distant metastases)
- Intercurrent illness that prevents further administration of treatment
- Unacceptable adverse event(s)
- Patient decides to withdraw from the study
- General or specific changes in the patient's condition render the patient unacceptable for further treatment in the judgment of the investigator
- Clinical progression
- Patient non-compliance
- Pregnancy (if applicable)
  - All women of child bearing potential should be instructed to contact the investigator immediately if they suspect they might be pregnant (e.g., missed or late menstrual period) at any time during study participation.
  - The investigator must immediately notify CTEP in the event of a confirmed pregnancy in a patient participating in the study.
- Termination of the study by sponsor

The reason(s) for protocol therapy discontinuation, the reason(s) for study removal, and the corresponding dates must be documented in the Case Report Form (CRF).

## 12.3 Follow-up

### 12.3.1 Duration of Follow- up (Please see study calendar in section 5.0 for complete list of follow-up tests and procedures)

|                                                                                                                                              | MRI rectum                                                                                                     | Endoscopy and digital rectal exam                                   | CT chest, abdomen, pelvis                                                   | CEA                                                                                         |
|----------------------------------------------------------------------------------------------------------------------------------------------|----------------------------------------------------------------------------------------------------------------|---------------------------------------------------------------------|-----------------------------------------------------------------------------|---------------------------------------------------------------------------------------------|
| All patients who completed pre-operative protocol treatment                                                                                  | Pre-treatment, post-TNT re-staging                                                                             | Pre-treatment, post-TNT re-staging                                  | Pre-treatment, Post-TNT re-staging, annually from 5 years post-registration | Pre-treatment, every 3-6 months post-TNT in Years 1-2, every 6 months post-TNT in Years 3-5 |
| All patients who are off pre-operative protocol treatment early due to Progression of disease-                                               | As per treatment team                                                                                          | As per treatment team                                               | As per treatment team                                                       | As per treatment team                                                                       |
| All patients who are off pre-operative protocol treatment early due to other reasons (patient refusal, clinician decision to withdraw/other) | As per treatment team                                                                                          | As per treatment team                                               | As per treatment team                                                       | As per treatment team                                                                       |
| Patients in WW group                                                                                                                         | After post-TNT re-staging: Q6 months in Years 1-2, Q12 months in Years 3-5 (As clinically indicated years 4-5) | Post-TNT re-staging: Q3 months in Years 1-2, Q6 months in Years 3-5 | Pre-treatment, Post-TNT re-staging, annually from 5 years post-registration | Pre-treatment, every 3-6 months post-TNT in Years 1-2, every 6 months post-TNT in Years 3-5 |

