**Evaluations during follow-up for WW patients (after completion of TNT with cCR and post-TNT restaging)**

| Years on study                                | Year 1
(Every 3 months) |   |   |    | Year 2
(Every 3 months) |    |    |    | Year 3
(Every 6 months) |    | Years 4-5**
(Every 6 months) |    |    |    |
|-----------------------------------------------|----------------------------|---|---|----|----------------------------|----|----|----|----------------------------|----|---------------------------------|----|----|----|
| Months after post-TNT restaging (+/- 30 days) | 3                          | 6 | 9 | 12 | 15                         | 18 | 21 | 24 | 30                         | 36 | 42                              | 48 | 54 | 60 |
| History and Physical                          | X                          | X | X | X  | X                          | X  | X  | X  | X                          | X  | X                               | X  | X  | X  |
| Sigmoidoscopy/
Proctosigmoidoscopy         | X                          | X | X | X  | X                          | X  | X  | X  | X                          | X  | X                               | X  | X  | X  |
| MRI Rectum                                    |                            | X |   | X  |                            | X  |    | X  |                            | X  |                                 | X  |    | X  |
| CT CAP                            |                            |   |   | X  |                            |    |    | X  |                            | X  |                                 | X  |    | X  |
| CEA levels                        | X                          | X |   | X  | X                          | X  |    | X  | X                          | X  | X                               | X  | X  | X  |

\*If TME completed via abdominoperineal resection – not relevant and unnecessary

\*\*MRI in years 4 through 8 would only be supported if clinically indicated by treating team.

 CT of the Chest, Abdomen and Pelvis Patients in the TME group will be followed according to NCCN guidelines.[1]

 After 36 months, CEA will be evaluated every 6 months up to five years, based on NCCN guidelines.

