## 8.2 Dose Modifications

The CTCAE v5.0 must be used to grade the severity of AEs. Refer to [http://ctep.cancer.gov/protocolDevelopment/electronic\\_applications/ctc.htm](http://ctep.cancer.gov/protocolDevelopment/electronic_applications/ctc.htm).

Deviations from the recommended treatment modifications/management must be documented in the patient treatment record.

In the event of disease recurrence, second primary colorectal cancer, or diagnosis of an invasive second primary/secondary malignancy, study therapy will be discontinued; further therapy is at the investigator's discretion. Tests, exams, and assessments **are required** and patients will continue to be followed off treatment for vital status per protocol.

If, in the opinion of the investigator, a toxicity is considered to be due solely to one component of the study treatment (i.e., 5-FU, capecitabine, oxaliplatin, or irinotecan) and the dose of that component is held or modified in accordance with the guideline below, the other components may be administered per protocol guidelines.

If several toxicities with different grades of severity occur at the same time, the dose modifications should be according to the highest grade observed.

Any chemotherapy doses that have been reduced may not be escalated.

**For any concomitant conditions apparent at baseline, the dose modifications will apply according to the corresponding shift in toxicity grade, if the investigator feels it is appropriate.** For example, if a patient has Grade 1 asthenia at baseline that increases to Grade 2 during treatment, this will be considered a shift of one grade and treated as Grade 1 toxicity for dose-modification purposes only.

**For specific questions or concerns regarding this section, please contact [name] [[contact]](mailto:[contact]) and/or [name] [mailto:[name]\\[contact]](mailto:[contact]).**  
In the event of treatment-related AEs during consolidation chemotherapy that requires treatment hold for  $\geq 30$  days from the date of the planned cycle, consolidation chemotherapy should be discontinued. If consolidation chemotherapy is discontinued because of delay, patients the subject should be referred for presurgical restaging as detailed in the study calendar in section 5.0

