## 12.4 Extraordinary Medical Circumstances

If, at any time the constraints of this protocol are detrimental to the patient's health and/or the patient no longer wishes to continue protocol therapy, protocol therapy shall be discontinued. In this event:

- Document the reason(s) for discontinuation of therapy on data forms.
- Follow the patient for protocol endpoints as required by the Study Calendar.

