### Follow-up for patients who are registered, but who never start study treatment

For all study participants who are registered to the trial but who never receive study intervention (regardless of eligibility), the follow-up requirements are specified below.

Randomized phase II and phase III: Baseline, off treatment, and post-treatment follow up (i.e., relapse, progression, and survival) data submission required. See the Data Submission Schedule accompanying the All Forms Packet.

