**Phase III Portion:**

The Phase III hypothesis testing analyses will be performed on ITT population. Sensitivity analyses will be performed on mITT and PP population. At interim and final analyses, stratified Cox model will be conducted to compare DFS in the experimental arm to DFS in the control arm with stratification factors as stratum, based on all data collected at the analysis time point.

- **Interim Analysis Decision Rule:** The interim analysis will be conducted when 50% of targeted events (about 143) which is estimated around 4.5 to 4.9 years after the first patient is randomized (about 3.6 to 8.4 months after all patients are enrolled). If the observed HR (stratified by stratification factors) at interim analysis is  $> 1.00$ , we will conclude that the chance of DFS in experimental arm being superior to that in control arm is too low. The results will be presented to Alliance DSMB and NCI for potential public release.
- **Final Analysis Decision Rule:** The final DFS analysis will be performed when at least 285 DFS events are observed combining the two arms. Stratified Cox model will be conducted to compare DFS in the experimental arm A to DFS in the control arm B. If the one-sided p-value of the comparison is  $< 0.025$ , then we will conclude the DFS in the experimental arm is superior to the control arm.

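### Sections 12.3.1 and 12.4 conflict on how early stoppers are assessed, which can bias phase III DFS if early stopping differs by arm

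*Combined protocol and SAP*

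**What the plan says.** **Section 12.3.1, follow-up table.** The row "All patients who are off pre-operative protocol treatment early due to other reasons (patient refusal, clinician decision to withdraw/other" has the entry "As per treatment team" in all four columns: MRI, endoscopy with digital rectal exam, CT, and CEA. The row "All patients who are off pre-operative protocol treatment early due to Progression of disease" has the same entries. The section heading refers to the Section 5.0 calendar for the full list of tests.

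**Section 12.4.** This covers patients for whom the protocol's constraints are detrimental and patients who no longer wish to continue protocol therapy. Once therapy is discontinued, the instruction is: "Follow the patient for protocol endpoints as required by the Study Calendar".

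**Section 5.0, follow-up calendars.** One is headed "Evaluations during follow-up for WW patients (after completion of TNT with cCR and post-TNT restaging"). The other is for TME patients after definitive resection and is not limited to patients who completed treatment.

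**Related rules.** Under Section 8.2, a patient whose consolidation chemotherapy is discontinued because of delay "should be referred for presurgical restaging as detailed in the study calendar in section 5.0". For registered patients who never start treatment, Section 12.5 has: "Baseline, off treatment, and post-treatment follow up (i.e., relapse, progression, and survival) data submission required".

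**Analysis.** Section 13.4.2 states: "The Phase III hypothesis testing analyses will be performed on ITT population". Section 13.1.1 lists four kinds of DFS event: death, local recurrence after an R0 TME, regrowth that cannot be removed with an R0 TME, and M1 disease. Section 13 gives no DFS censoring rule and no rule for missed assessments.

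**The concern.** A site with a patient who refuses further chemotherapy can follow either section and be compliant, so practice may vary between sites. Three of the four kinds of DFS event are found only if someone looks. Death is the exception. Patients who complete treatment are looked at on a fixed schedule. Early stoppers may be looked at as often, less often or more often.

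All of them count in the primary DFS comparison. If early stoppers' events are missed or found late, and one arm has more early stoppers, that arm's DFS looks better than it is. The trial is open to this because the arms differ in chemotherapy intensity. Section 13.5.1 accordingly monitors early stopping, to keep the comparison between arms meaningful.

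**Working it through.** **1. Which rule covers whom**

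| Patient off treatment early, no DFS event | 12.3.1 table | 12.4 | Section 5.0 follow-up calendar |
|---|---|---|---|
| Has TME | treatment team | Study Calendar | TME calendar fits |
| No TME, on watch and wait | treatment team (the separate WW row is not limited to completers) | Study Calendar | WW heading requires completed TNT with cCR |
| No TME, not on watch and wait | treatment team | Study Calendar | neither heading fits |

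In the last row, Section 12.4 points to a calendar that does not exist for that patient. Section 8.2 adds one restaging visit, and only after a stop for delay. Section 12.5 asks for data from patients who never start, but submitting data does not schedule a scan. The progression row is not wholly harmless either: local progression alone is not among the DFS events in Section 13.1.1, so a patient can be in that row and still be event-free.

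**2. The planned sensitivity analyses do not test this**

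Under Section 13.4.1, mITT keeps anyone who completed LCRT and had one chemotherapy dose. PP keeps eligible patients with at least three cycles. A patient who stops after cycles 3 to 7 can be in ITT, mITT and PP alike.

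**3. The plan's own figures**

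- Events for HR 0.70, 85% power, one-sided 0.025: 4 × (1.960 + 1.036)² / (ln 0.70)² = 4 × 8.98 / 0.1272, or 283. The plan has 285.
- Power at 285 events: (√285 / 2) × 0.3567 − 1.960 = 3.011 − 1.960 = 1.051, which is 85.3% (85.1% with the futility stop).
- Experimental 3-year DFS: 0.76^0.70 = 82.5%, as stated.
- Exponential DFS, 180 patients per year and four years' minimum follow-up give about 284 events from 760 patients.
- Early-off-treatment (EOT) rule, 131 per arm, 7% against 17%, one-sided 0.05: 80.4% power. The plan has 80%.

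**4. Size of the possible bias**

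Assumptions that are not in the documents: 17% of triplet and 7% of doublet patients are off schedule. Here 7% is the OPRA reference in Section 13.5.1, and the extra 10 points are the difference that sizes the EOT rule. Let m be the share of these patients' DFS events that are never recorded while the patient stays in the risk set. Then

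- HR multiplier k = (1 − 0.17m) / (1 − 0.07m)
- one-sided type I error = P(Z > 1.96 + 8.441 × ln k), where 8.441 = √285 / 2.

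| m | k | Type I error | Observed HR if true HR is 0.70 |
|---|---|---|---|
| 10% | 0.983 / 0.993 = 0.990 | 0.030 | 0.693 |
| 25% | 0.9575 / 0.9825 = 0.975 | 0.041 | 0.682 |
| 50% | 0.915 / 0.965 = 0.948 | 0.065 | 0.664 |

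A log-rank simulation (16,000 trials per setting, analysed at 285 recorded events, 85% of early stoppers' events assumed to depend on assessment) gives HR 0.946 and type I error 0.068 at m = 50%. There m applies only to the 85%, so 42.5% of these patients' events are lost. The formula at 42.5% gives 0.9278 / 0.9703 = 0.956, so it slightly understates the effect.

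Other settings:

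- Events recorded late, not lost (simulation): a 6-month delay gives HR 0.989 and type I error 0.031. A 12-month delay gives 0.979 and 0.036.
- Equal stopping, 7% in both arms: k = 1, no bias.
- Reversed stopping (7% triplet, 17% doublet), m = 50%: k = 0.965 / 0.915 = 1.055, type I error 0.008, power 73%.
- Detection 3 months earlier in early stoppers (simulation): HR 1.006.
- An excess of 6.7 points, the last EOT review threshold (13.7% against 7%): type I error 0.035 at m = 25% and 0.048 at m = 50%.

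**The case against.** The strongest case against is that much of this is covered. The 12.3.1 heading defers to the Section 5.0 calendar, Section 12.4 reaches refusals and patients harmed by treatment, resected patients have the TME calendar, and Section 6.1.4 requires reports at recurrence. Leaving assessment to the treatment team does not mean less assessment. This stands to the extent that under-ascertainment is a risk and not a stated fact. It does not remove the conflict or supply a calendar for the early stopper without TME.

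The second objection is that the EOT rate is a poor measure of the 12.3.1 row. EOT includes progressions and deaths, where a DFS event has often already occurred. It excludes withdrawals unrelated to disease, whereas the row names refusal. It counts anyone with fewer than eight cycles, many of whom will be restaged and join a calendar, and its denominator is patients who completed LCRT and started chemotherapy. This stands, and the 17% and 7% are illustrative only. If half of these patients joined a calendar (assumed), the shares are 8.5% and 3.5%. At m = 30%, k = 0.9745 / 0.9895 = 0.985 and type I error is about 0.034.

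Third, late detection is more plausible than permanent loss, given four years' minimum follow-up and death as an event. This is fair, and the delay figures are small.

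Finally, the EOT rule would prompt a review of a large imbalance. But its last look is at 262 of 760 patients, and it reviews treatment completion, not DFS ascertainment.

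**Conclusion.** The conflict between Sections 12.3.1 and 12.4 is on the page, as are the calendar gap and the absence of a DFS censoring rule. All three touch the primary phase III endpoint. The bias is conditional: it needs unequal early stopping and missed or late events. Under the assumed 17% against 7%, one-sided type I error would be about 0.030 to 0.065 with 10% to 50% of early stoppers' events lost, and 0.031 to 0.036 with a 6 to 12 month delay. If off-schedule patients were instead censored at their last assessment, bias would arise only if their prognosis differed from that of patients still followed. The plan does not say which applies.

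A reader might infer that early stopping is expected to be 17% against 7%, and so that the HR is biased toward the triplet. The documents do not support that. The 10-point difference is the alternative that sizes a monitoring rule, and no forecast for the triplet arm is given. Equal stopping gives no bias, and reversed stopping works against the triplet and costs power. This should be corrected while patients are still being followed, because missed assessments cannot be recovered at analysis.

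**What to change.** 1. Reconcile Section 12.3.1 with Section 12.4. Every randomised patient without a DFS event who has not withdrawn consent for follow-up should have DFS status assessed at the intervals of an existing Section 5.0 follow-up calendar.
2. State which calendar, and which starting point within it, applies to an early stopper who does not have TME.
3. Limit the treatment-team entry to patients who already had a DFS event or withdrew consent for follow-up.
4. In Section 13.4.2, add a DFS censoring rule, including how missed assessments are handled, and a sensitivity analysis for patients assessed off schedule.

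This concerns endpoint assessment only, and treatment decisions stay with the treating team. It does not require one common time origin for all patients: the WW and TME calendars count from different points and use different tests, and aligning them would redesign surveillance for everyone. With assessment independent of treatment status, the multiplier is 1.00 and the design keeps its 0.025 type I error and about 85% power at 285 events and 760 patients. The cost is a reworded table, a short addition to the analysis section, and some extra follow-up and data collection in off-treatment patients.

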## 12.4 Extraordinary Medical Circumstances

If, at any time the constraints of this protocol are detrimental to the patient's health and/or the patient no longer wishes to continue protocol therapy, protocol therapy shall be discontinued. In this event:

- Document the reason(s) for discontinuation of therapy on data forms.
- Follow the patient for protocol endpoints as required by the Study Calendar.

## 12.5 Managing ineligible patients and registered patients who never receive protocol intervention

### Definition of ineligible patient

A study participant who is registered to the trial but does not meet all of the eligibility criteria is deemed to be ineligible.

### Follow-up for ineligible patients who discontinue protocol treatment

For patients who are deemed ineligible after registering to the trial, who start treatment, but then discontinue study treatment, the same data submission requirements are to be followed as for those patients who are eligible and who discontinue study treatment.

### Follow-up for patients who are registered, but who never start study treatment

For all study participants who are registered to the trial but who never receive study intervention (regardless of eligibility), the follow-up requirements are specified below.

Randomized phase II and phase III: Baseline, off treatment, and post-treatment follow up (i.e., relapse, progression, and survival) data submission required. See the Data Submission Schedule accompanying the All Forms Packet.

## 13.0 STATISTICAL CONSIDERATIONS

### 13.1 Study Endpoints

#### 13.1.1 Primary Endpoints:

- **Phase II:** The primary endpoint is cCR rate. The cCR rate is defined as the number of patients who achieved cCR at the end of TNT divided by number of patients included in the analysis population (see Section 13.4.1). This endpoint will be assessed within 8-12 weeks after completion of TNT. If there is a cCR, then the patient will be counted in the numerator. If there is a near-complete response (nCR) then a re-evaluation within 4-8 weeks will be performed. If the tumor has evolved to a cCR, then the patient will be counted in the numerator. Otherwise, the patient will be deemed as NOT achieving cCR status.
- **Phase III:** Disease-free survival (DFS): is defined as the time from date of randomization to the date of first occurrence of the following events:
  - Death due to all causes
  - Tumor that recurs locally after an R0 TME
  - Tumor that regrows after an initial apparent clinical and radiological CR and cannot be surgically removed with an R0 TME\*
  - M1 disease diagnosed at any point after the initiation of treatment

\* Regrowth for patients who are on watch and wait approach (regardless of treatment assignment) that can be surgically removed with an R0 TME will NOT be a DFS event

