### 7.3 Surgery

All patients will undergo assessment at 8-12 weeks post-TNT completion. If patients have a cCR (no tumor on endoscopy, MRI, or clinical exam using the MSK regression schema) then patients may be offered a WW approach or TME depending on the outcome of a thorough discussion with their treating physician concerning the risks and benefits of each approach and both they and their physician agree with the intended approach. If the patients have an incomplete response (any evidence of residual tumor by endoscopy, MRI or clinical exam using the MSK regression schema) then they be recommended to undergo TME (not mandated and identical to OPRA). Of note, and as in OPRA, if patients have a near complete response (nCR) then patients can undergo a repeat assessment 8 weeks later (+/-2 weeks). If there is any evidence that the tumor has stopped responding, persists or regrows then the patient will be recommended to undergo TME (e.g. nCR that fails to evolve to a cCR at 20 weeks (+/- 4 weeks) post-completion of TNT OR local regrowth after initial cCR determination). If there is a discrepancy between MRI and endoscopy/DRE then endoscopy/DRE should take precedence in the decision making on whether to proceed to WW or TME.

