##### Overall Completeness of TME Resection:

This categorization schema should focus on the pelvic resection of the TME specimen. If distant tumor is appreciated intraoperatively (for example, a liver metastasis), the pelvic resection may still be considered R0.

|              |                                                                                                                                                                                                                                                                                                                                                                                                                                                                                                                                                         |
|--------------|---------------------------------------------------------------------------------------------------------------------------------------------------------------------------------------------------------------------------------------------------------------------------------------------------------------------------------------------------------------------------------------------------------------------------------------------------------------------------------------------------------------------------------------------------------|
| R0 resection | All gross disease has been removed, and microscopic examination reveals all surgical margins free of tumor. This must include the proximal, distal and radial margin.
Tumor > 1mm from the tumor resection margins is considered R 0 . In some cases, intraoperatively, a surgeon may biopsy a liver nodule or retroperitoneal node. Resection will still be considered curative if pathologic examination reveals positive lymph nodes as long as the nodes were completely resected, unless there is also evidence of positive margins. |
| R1 resection | There is evidence of tumor manifest at 1 or more surgical resection margins based on microscopic pathologic assessment of the tumor specimen but there is no macroscopic evidence of tumor at any resection margin nor is there macroscopic evidence of residual tumor based on the surgeon's operative report.                                                                                                                                                                                                                                         |

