### 11.4 Disease Evaluation after TME

Disease evaluation for all patients after completion of surgery. Patients will be evaluated as per the schedule of tests noted in Section 5.0. At the time of evaluation, patients will be classified in the following manner:

- No evidence of disease (NED)
- Recurrence of disease (REC): The appearance of rectal carcinoma in the primary site, nodal basin or distant organ sites during follow-up will be classified as recurrence cancer. Recurrence will be classified as local or distant.

|                           |                                                                                          |
|---------------------------|------------------------------------------------------------------------------------------|
| Local recurrence   | Any tumor located in the pelvis or the perineal scar after TME has been completed |
| Distant recurrence | Any tumor outside the pelvis and the perineal scar; can occur prior to or after TME      |

Patients may have local recurrence, distant recurrence, both or neither. Imaging should be used to document the extent of local and distant disease recurrence. Pathological confirmation of suspected distant metastasis should be performed based on clinical judgment and is not mandated.

Although pathologic confirmation of recurrence is not mandated, local and distant recurrences will be categorized based on supporting evidence. Recurrences will be categorized based on whether they are evident from:

|                             |                                                                                                                                                                                                        |
|-----------------------------|--------------------------------------------------------------------------------------------------------------------------------------------------------------------------------------------------------|
| Pathology:           | Use this category if there is any pathology or cytology demonstrating recurrent rectal cancer.                                                                                                         |
| Serial Imaging:      | Use this category is for recurrences that have not been confirmed by pathology but where serial imaging studies (serial is defined as similar scans performed more than 30 days apart) indicate tumor. |

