## 12.0 END OF TREATMENT/INTERVENTION

### 12.1 Duration of Protocol Treatment

During neoadjuvant treatment, protocol treatment (intervention) is to continue until completion of LCRT and 8 cycles of consolidation chemotherapy, distant disease progression, local/regional disease progression which precludes surgery, or unacceptable adverse events. After neoadjuvant treatment, TME will be performed when it is appropriate (incomplete response to assigned TNT regimen (e.g. residual tumor remains, no evolution to complete response). Please see the study calendar (Section 5) and the treatment section (Section 7) for treatment and follow-up time periods.

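### The phase III DFS event list omits non-R0 surgery, pelvic tumor after it, and unresectable local progression in patients who never had a complete response

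*Combined protocol and SAP*

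**What the plan says.** Section 13.1.1 defines phase III DFS from randomization to the first of four events. Two of them can occur in any patient: "M1 disease diagnosed at any point after the initiation of treatment" is one, and the other is "Death due to all causes". The remaining two cover local failure. The first of these is "Tumor that recurs locally after an R0 TME". The second, which is limited to patients who had already responded, is "Tumor that regrows after an initial apparent clinical and radiological CR and cannot be surgically removed with an R0 TME". A footnote adds that regrowth on watch-and-wait that is removed with an R0 TME is not an event.

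Other sections recognize states that the list does not reach. Section 12.1 names "local/regional disease progression which precludes surgery", but only as a reason to end protocol treatment, and Section 12.2 does the same. Section 11.3.1 defines R1 ("There is evidence of tumor manifest at 1 or more surgical resection margins based on microscopic pathologic assessment"), R2 and no resection. Section 11.4 defines local recurrence as "Any tumor located in the pelvis or the perineal scar" once TME has been completed, whatever the margin status. Section 7.3 recommends TME for incomplete response but does not mandate it, and lets a patient with cCR choose TME.

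**The concern.** A failed R0 resection is an event only if a complete response and a regrowth came first. Patients who go straight to surgery because they did not respond can have known residual or unresectable tumor and still be carried at risk as disease-free. Identical surgical findings are then scored differently according to the route to the operating room, and that route depends on response, which the experimental treatment is meant to change.

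This is the phase III primary endpoint. It determines which patients make up the 143 events at the futility look and the 285 at the final analysis, and the absolute DFS rates that will be reported. The mismatch with Section 11.4 also means that pelvic tumor after an R1 TME is a recurrence under one section and not a DFS event under another, so it could be coded either way.

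**Working it through.** **1. Apply the list by pathway.**

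| Finding | After CR and watch-and-wait | Never a CR |
|---|---|---|
| TME is R1 or R2 | Event | No event |
| Pelvic tumor after an R0 TME | Event | Event |
| Pelvic tumor after a non-R0 TME | Already an event at the failed resection | No event |
| Local tumor that cannot be resected | Event | No event |
| M1 disease or death | Event | Event |

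No other section fills the three empty cells. A patient with residual tumor and no prior CR who declines TME is also outside the list.

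**2. Reproduce the plan's figures (13.3.2).** Schoenfeld events for HR 0.70, one-sided 0.025, 85% power, 1:1: 4(1.960 + 1.036)² / (ln 0.70)² gives 283, against 285 stated. Power at 285 events is 0.853, or 0.851 allowing for the futility look. 0.76^0.70 = 0.825, as stated. Exponential DFS with 760/180 = 4.22 years of accrual and 4 more years of follow-up gives 284 expected events. The sample-size arithmetic is sound.

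**3. Patients exposed to the gap.**
- Design cCR rates (13.3.1): control 380 × 0.50 = 190; experimental 380 × 0.33 = 125; total 315.
- Smallest cCR difference that succeeds in phase II (9.3 points, 13.4.2), control at 50%: 190 and 380 × 0.407 = 155.
- OPRA watch-and-wait entry (13.5.1): 166 − 120 = 46 of 166 (27.7%) did not enter, so about 380 × 0.277 = 105 control patients. This takes entry as a stand-in for initial CR. It matters because the 52.4% behind the 50% assumption is 87/166, and 120 − 33 regrowths = 87, so that benchmark already excludes patients who responded and then regrew.

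**4. Non-R0 resections affected.** The documents give no R0 rate for direct TME. I borrow 6% and 17%, the complements of the 94% and 83% R0 rates that 13.5.1 uses for salvage TME on watch-and-wait. This is an assumption, as are TME in every exposed patient and equal rates in the two arms.

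| Assumed rate | Control (of 190) | Experimental (of 125) | Total | Share of 285 | Control, OPRA entry (of 105) |
|---|---|---|---|---|---|
| 6% | 11 | 8 | 19 | 7% | 6 |
| 10% | 19 | 13 | 32 | 11% | about 11 |
| 17% | 32 | 21 | 54 | 19% | 18 |

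Patients who later have M1 disease or die are counted, but late. Unresectable progression is not in these figures.

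**5. Effect on the hazard ratio.** In 400 simulated trials per scenario, the same patients were analyzed with and without the omitted failures. Assumptions: exponential listed events, control hazard −ln(0.76)/3 = 0.0915 per year; failure in 6% or 17% of patients without cCR, dated at 0.85 years; afterwards, 1 or 5 times the arm's listed-event hazard. Each row covers four combinations.

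| Listed-event HR; cCR control/experimental | HR, present list | HR, failures added | Largest change |
|---|---|---|---|
| 0.70; 50/67% | 0.685-0.701 | 0.684-0.698 | 0.016 |
| 1.00; 50/67% | 0.963-1.006 | 0.935-0.981 | 0.061 |
| 1.00; 50/50% | 0.992-1.007 | 0.990-1.006 | 0.008 |
| 0.70; 50/50% | 0.693-0.718 | 0.712-0.742 | 0.045 |

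In the first row, which is the design hypothesis, adding the failures gives a net 3 to 33 more events by the end of follow-up; the rest were already counted late.

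**The case against.** The strongest reply is that the list is arm-neutral, the event count and power reproduce, and M1 disease and death count for everyone, so many of these failures are delayed rather than lost. The 76% control rate comes from OPRA, and a broader definition loosens that link. All of this stands.

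A reader might go further and infer that the omission differs by arm and pulls the HR toward 1. The documents do not support that as a fact. Unequal exposure follows only if cCR differs as hypothesized and failure rates among non-responders are similar; a triplet-arm rate about 1.5 times control (0.50/0.33) would equalize the counts. On the design figures the HR barely moves, because the ratio of omitted events (0.66) is close to the design HR (0.70). Away from the design, the direction varies: with higher cCR and no effect on listed events the omission hides a small benefit; with an effect on listed events and equal cCR it flatters the experimental arm.

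Nor are 6-17% the plan's figures for direct surgery, and 190 exposed control patients may be too many.

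The objection does not fill the gap. A small HR effect does not justify carrying patients with known residual tumor as disease-free, or reconcile 13.1.1 with 11.4.

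**Conclusion.** The gap stands on the text: without a prior CR, a non-R0 TME, pelvic tumor after it, and local progression that precludes resection are not DFS events until M1 disease or death, while the equivalent failure after watch-and-wait is. The conflict with 11.4 also stands. Neither depends on any assumed rate.

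The size is uncertain. Across both arms it is about 19-54 non-R0 resections uncounted or late, assuming 6-17% non-R0, the design cCR rates, and TME in every patient without cCR; in the control arm alone it is about 6-18 if exposure follows OPRA entry. The HR effect is about 0.02 or less under the design hypothesis. The problem is therefore what the primary endpoint measures and how consistently events are classified. It is not a sample-size error or a demonstrated bias between arms.

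**What to change.** By protocol amendment, before the 143-event interim analysis:

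- In 13.1.1, drop the R0 condition from local recurrence after TME, so that it matches 11.4.
- Add, regardless of prior CR, locoregional progression that precludes R0 resection (dated at documentation) and non-R0 TME (dated at surgery).
- Keep R0-salvaged regrowth as a non-event.
- State how residual tumor with TME declined is counted and dated.
- Report the present definition as a sensitivity analysis.

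Little or no new data collection should be needed: 11.3 already requires operative and pathology reports with margin involvement, and 6.1.4 requires documentation of progression, recurrence and surgical outcome. The costs are an amendment to the primary endpoint, somewhat more and earlier events, and less direct comparability with the OPRA-based 76% control rate, which 13.3.2 should acknowledge. Because 11.1 does not require central radiology review, whether progression precludes resection would rest on local judgment, so the amendment should say what documentation supports that call.
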